### Recruitment

All patients who will undergo laparoscopic or robotic-assisted APR or low Hartmann’s procedure for rectal adenocarcinoma at each study site are considered for the trial at the time of their visit to the outpatient department prior to surgery. After receiving the proper information on the possible advantages and disadvantages of the intervention, and voluntarily signing an informed consent form, the subject is enrolled in the Chimney Trial. Participating investigators are qualified colorectal or general surgeons experienced in the surgical management of patients with colorectal adenocarcinoma and either laparoscopic or robotic-assisted APR or low Hartmann’s procedure. Each hospital’s contribution to the study is limited to no less than 20 cases. The enrollment will last for approximately 2 to 3 years in attending hospitals.

## Methods

### Allocation

All analyses will be performed by or under the guidance of professional statisticians and following the CONSORT guidelines [26].

Patients are randomly allocated to the study group according to a computer-generated list, compiled by a biostatistician who is not involved in the clinical care of trial patients. The randomization is performed in blocks, where the block size varies randomly between two, four, and six patients. A separate randomization list is created for each center. The software designed for the study is used to randomize the patients. After confirmation of patients’ eligibility and their willingness to participate, the randomization is completed at the outpatient visit prior to surgery and the patients are kept blinded to study technique.

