### Sample size

To calculate a sample size needed to compare the two groups, we estimated a 6.4% rate of PSH and 34% PSH on a CT scan for the PVDF-mesh group and control group during 12 months’ follow-up [21, 23]. Assuming α = 0.05 and power = 90%, we would need 51 patients per group. Furthermore, assuming a 5-year drop-out rate of 50%, 102 patients per group are needed to reach statistically significant results also during long-term follow-up.

All analyses will be performed by, or under the guidance of, professional statisticians and following the Consolidated Standards of Reporting Trials (CONSORT) guidelines [26].

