### Blinding

Patients are blinded to the randomization group during their primary stay at the hospital. For safety reasons, their group designation is stated in the patients’ medical files for direct access in case of complications. The patient has direct access to their medical records after hospitalization and, therefore, the blinding is not possible to maintain. Patients are assigned at the control visits by a surgeon not involved in the study and without accessing the randomization group. The independent radiologists analyze the CT scan without access to the randomization group information.

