### Statistical methods

The primary endpoint will be the incidence of PSHs detected by CT scan with 95% confidence intervals for all groups at 1-year follow-up. Secondary outcomes are the incidence of PSHs at 3- and 5-year follow-ups and the development of quality of life during the follow-ups. The analyses will be based on the intention-to-treat principle. The primary endpoint and other categorical data will be analyzed by the χ^2^ test or Fisher’s exact test. Analysis of variance (ANOVA) will be used for continuous variables. For repeatedly measured data, the linear mixed model (LMM) will be used for continuous data and the generalized linear mixed model (GLMM) will be used for categorical data. Multiple imputations of missing outcome data will be used for sensitivity analyses. The SPSS statistical programs (IBM Corp. 2016. IBM SPSS Statistics for Windows, Version 24.0. Armonk, NY, USA) and SAS (version 9.4, SAS Institute Inc., Cary, NC, USA) will be used for the analyses.

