## Discussion

The aim of this study is to assess, in a randomized, multicenter setting, the safety and efficiency of specially designed, funnel-shaped PVDF mesh (DynaMesh®-IPST, FEG Textiltechnik GmbH, Aachen, Germany) in PSH prevention compared with a control group without a mesh, all being operated on using mini-invasive laparoscopic/robotic methods. The hypothesis is that the high incidence of up to 32% of PSHs detected on CT scans after retromuscular sublay mesh [21] can be reduced and further repair of PSHs can be prevented with the use of a chimney-like tube in the PVDF mesh.

Research on specially designed PVDF mesh as prophylaxis is limited but promising with a PSH incidence rate of 6.4% at 1-year-CT follow-up [23]. No RCTs using this mesh exist so far. All previous case series [22–24] included a small number of patients with no controls thus providing inadequate evidence for efficiency and safety for more routine use of this prophylactic mesh.

The focus of the current study is on the incidence of PSHs at both short- and long-term follow-up.

PSHs are not only graded by European Hernia Society Classification [25], but also the exact size and content of hernias upon the Valsalva maneuver are measured as well as the development of measurements throughout the follow-up. Radiological risk factors for PSH development will be determined as part of radiological follow-up. All symptoms caused by a stoma itself or a PSH are recorded to analyze the clinical significance of clinically or radiologically detected PSHs. The quality of life is measured by both RAND-36 and the colostomy impact score and recorded throughout the follow-up period as part of defining the clinical significance of PSHs. The re-operation rate and operations done for PSH are recorded in both groups.

This trial is designed as a single-blinded study for safety reasons. In the case of serious complications demanding re-operation, it is crucial for decision-making purposes to always have instant access to all technical aspects of the surgery. Patients are blinded to the method used during their hospital stay. Unfortunately, it is impossible to blind patients beyond that time due to direct access to the national medical database including all medical records and hospital stays.

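### Randomisation at the outpatient visit comes before three exclusions that only surgery or the postoperative stay can reveal, so the exclusion list conflicts with the intention-to-treat analysis

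*Protocol article*

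**What the plan says.** The Allocation section fixes the order of events. "After confirmation of patients’ eligibility and their willingness to participate", it says, "the randomization is completed at the outpatient visit prior to surgery".

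The Exclusion criteria section mixes two kinds of criterion. Most can be settled in clinic (ASA class, previous malignancy, pregnancy, language). Three cannot:

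- conversion to an open operation, known only during surgery;
- abdominal infection that is active when the operation takes place, known at or shortly before surgery;
- a complication on the surgical ward that requires a laparotomy, known only after the allocated treatment has been given.

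On knowledge of the allocation, the Blinding section says "Patients are blinded to the randomization group during their primary stay at the hospital" and adds that "their group designation is stated in the patients’ medical files for direct access in case of complications". The follow-up surgeon and the radiologists also work without it. The Discussion confirms: "This trial is designed as a single-blinded study for safety reasons". The operating surgeon is not listed among those blinded.

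On analysis, the Statistical methods section says: "The analyses will be based on the intention-to-treat principle". The article does not say whether a patient who meets one of the three late criteria is kept, removed or replaced.

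**The concern.** The stated rules cannot all be followed. If eligibility must be confirmed before randomisation, the three late criteria cannot be eligibility criteria. If they are applied as exclusions, patients leave after randomisation and the analysis is no longer by intention to treat.

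Two things are at stake. The first is comparability of the arms. Randomisation protects the comparison only for the full randomised set. Exclusions made after allocation, by staff who may know it, can differ between arms in number or in type of patient.

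The second is the safety comparison. A laparotomy for a complication on the ward happens after the mesh has or has not been placed, and it may be a consequence of the mesh. The same event belongs to the secondary outcomes (30-day Clavien-Dindo complications, reoperation rate). It is also the kind of event that the Clavien-Dindo 3B stopping rule in the Trial design section exists to count. Excluding these patients could remove harm from the very comparison meant to detect it.

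**Working it through.** **Inputs from the protocol article.** Rates: "we estimated a 6.4% rate of PSH and 34% PSH on a CT scan for the PVDF-mesh group and control group". Size: "Assuming α = 0.05 and power = 90%, we would need 51 patients per group", doubled to 102 per group for 50% drop-out at 5 years. Allocation is 1:1. Sidedness is not stated; two-sided is assumed. No conversion, infection or re-laparotomy rate is given, so every exclusion fraction below is an assumption.

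**1. The plan's own figure.** Two-proportion formula with p1 = 0.34, p2 = 0.064 and mean p = 0.202:

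n = [1.960 × √(2 × 0.202 × 0.798) + 1.282 × √(0.34 × 0.66 + 0.064 × 0.936)]² / 0.276² = 42.4, so 43 per group.

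With continuity correction: (42.4/4) × [1 + √(1 + 4/(42.4 × 0.276))]² = 49.3, so 50, against the stated 51. Drop-out: 51/(1 − 0.5) = 102, exact. The sample size is not in dispute.

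**2. How many patients might be affected.** If 5%, 10% or 15% of the 204 randomised patients met a late criterion: 204 × 0.05 = 10, × 0.10 = 20, × 0.15 = 31.

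**3. Removal from one arm only, with no true effect.** True risk is 34% in both arms; 10 of 102 are removed from one arm, and those removed have risk q. The observed rate is (102 × 0.34 − 10q)/92 = (34.68 − 10q)/92. The type I error is the normal-approximation rejection probability of the pooled two-sided 5% test with 92 against 102 patients.

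| q in those removed | Observed rate | Type I error |
|---|---|---|
| 34% (same as the rest) | 34.0% | 5.0% |
| 50% | 32.3% | 5.7% |
| 68% (doubled) | 30.3% | 8.5% |
| 100% (bound) | 26.8% | 19.0% |
| 0% (bound) | 37.7% | 8.4% |

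**4. Equal removal from both arms.** Under no effect, removing 10 doubled-risk patients from each arm gives 30.3% in both, so the difference is zero and the type I error stays at 5%. At the planned rates, control falls to 30.3% and mesh to (102 × 0.064 − 10 × 0.128)/92 = 5.7%. The difference is then 24.6 points instead of 27.6.

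**5. Limits in the mesh arm.** At 6.4%, removing 10 hernia-free patients raises the rate only to 6.528/92 = 7.1%.

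**6. Cost of keeping everyone.** If a fraction c of the mesh arm receives no mesh and has the control risk, the mesh-arm rate is 0.064(1 − c) + 0.34c.

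| c | Mesh-arm rate | Power, 102 per arm | Power, 51 per arm |
|---|---|---|---|
| 10% | 9.16% | 99.3% | 87.3% |
| 20% | 11.92% | 96.8% | 76.3% |

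**7. The stopping rule.** Taking the first safety look as 30 patients per group, the 10% limit is 3 patients. If one of three patients with a serious complication is excluded because that complication needed a laparotomy, the group shows 2/29 = 6.9%, or 2/30 = 6.7% if replaced, and the limit is not reached.

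**The case against.** A reader might infer that these patients are in fact dropped from the analysis. The documents do not establish that. Intention to treat is stated, data up to withdrawal are to be analysed, exceptions to the protocol are to be recorded, and the flow chart and any analysis plan are not shown. This stands: removal is what the exclusion list implies, not a stated rule. It does not resolve the conflict, because the exclusion list and the intention-to-treat sentence are both printed and point in opposite directions.

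A reader might also infer that surgeons exclude patients in full knowledge of the arm. The article does not say when the operating surgeon learns the allocation. The surgeon must place or omit the mesh, is not named as blinded, and could read the file. Knowledge before a decision to convert is therefore possible, even likely, but not documented. There is also no evident reason why the arm should change that decision, since the mesh is placed only at stoma formation. For conversion and infection, then, the case rests on opportunity, not on a shown mechanism. For postoperative laparotomy it does not need the surgeon's knowledge at all: the treatment itself can cause the event.

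It would also overstate the matter to say that observed rates could shift by several points either way in both arms. Steps 3 and 5 show that this is possible at 34%, but in the mesh arm at 6.4% the rise is capped at 0.7 points when 10 patients are removed. Dilution from keeping converted patients is not a serious problem at 102 per arm.

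**Conclusion.** The conflict is real and lies in the text: three exclusions cannot be confirmed at the time fixed for randomisation, and applying them afterwards contradicts intention to treat. The postoperative-laparotomy criterion is the most serious, because it conditions on an event that may follow from the mesh and that overlaps the complication outcomes, the reoperation outcome and the stopping rule.

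The likely bias in the primary endpoint cannot be sized from the document. It ranges from none, if removal is unrelated to arm, to a type I error of about 8.5% if 10 of 102 patients at doubled risk leave one arm only. Those fractions and risks are assumptions. This should be corrected by amendment; it does not invalidate the design or the sample size.

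**What to change.** 1. Delete the postoperative-laparotomy item from the exclusion criteria and report the event as an outcome, by arm.
2. State that every randomised patient, including those converted, found infected or re-operated by laparotomy, stays in the intention-to-treat and safety sets, and that these events are reported by arm. This costs a sentence or two, and power remains about 99% at 102 per arm if 10% of the mesh arm receive no mesh.
3. For patients not yet randomised, preferably keep consent at the clinic but complete the browser-based randomisation in theatre, once the minimally invasive resection is finished and infection is ruled out, before the stoma is formed. Conversions then become screen failures. The two arms differ only by the mesh, so the allocation is not needed earlier.

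Item 3 has costs: a mesh must be available for every case and someone must log in during surgery. Recruitment began in February 2019, so the change would also mix two randomised populations; patients randomised before and after it should be distinguished in a sensitivity analysis. Item 3 does not cure the postoperative criterion, so items 1 and 2 are needed in any case.

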### Blinding

Patients are blinded to the randomization group during their primary stay at the hospital. For safety reasons, their group designation is stated in the patients’ medical files for direct access in case of complications. The patient has direct access to their medical records after hospitalization and, therefore, the blinding is not possible to maintain. Patients are assigned at the control visits by a surgeon not involved in the study and without accessing the randomization group. The independent radiologists analyze the CT scan without access to the randomization group information.

### Data collection, management and analysis

A dedicated electronic database and randomization software program is used to host the clinical trial data for this study. All electronic case report forms (eCRFs) are handled with a special trial ID. Access to the database is limited to the main investigators. All data requested on the eCRFs will be recorded. All missing data will be explained.

Data collection is the responsibility of the principal investigator at each study site and is reviewed by the study group.

Reasons for withdrawal will be documented carefully. The investigator will attempt to contact the subjects at least three times prior to designating them as lost to follow-up. The investigator will document the date and type of attempted communication. If a subject cannot be reached during the visit window, a missed visit is recorded; after three consecutive missed visits, a subject is considered lost to follow-up and a study exit form will be completed on the electronic database. Any data on a subject’s participation and procedures until the withdrawal will be analyzed within the research.

All complications are recorded and monitored using a specific eCRF. Data of all complications is later published as part of the trial results.

### Statistical methods

The primary endpoint will be the incidence of PSHs detected by CT scan with 95% confidence intervals for all groups at 1-year follow-up. Secondary outcomes are the incidence of PSHs at 3- and 5-year follow-ups and the development of quality of life during the follow-ups. The analyses will be based on the intention-to-treat principle. The primary endpoint and other categorical data will be analyzed by the χ^2^ test or Fisher’s exact test. Analysis of variance (ANOVA) will be used for continuous variables. For repeatedly measured data, the linear mixed model (LMM) will be used for continuous data and the generalized linear mixed model (GLMM) will be used for categorical data. Multiple imputations of missing outcome data will be used for sensitivity analyses. The SPSS statistical programs (IBM Corp. 2016. IBM SPSS Statistics for Windows, Version 24.0. Armonk, NY, USA) and SAS (version 9.4, SAS Institute Inc., Cary, NC, USA) will be used for the analyses.

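### For long-term reoperations, readmissions, stoma complications and operation-free survival, the methods section names no analysis that uses time at risk, although the plan expects half the patients to drop out by 5 years

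*Protocol article*

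**What the plan says.** All references are to the protocol article.

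- **Statistical methods.** The test is set in one sentence: "The primary endpoint and other categorical data will be analyzed by the χ^2^ test or Fisher’s exact test". The population is set in another: "The analyses will be based on the intention-to-treat principle". For data measured repeatedly, "the generalized linear mixed model (GLMM) will be used for categorical data". On missing outcomes: "Multiple imputations of missing outcome data will be used for sensitivity analyses". No Kaplan-Meier, log-rank, Cox, cumulative-incidence or person-time method is named.
- **Outcomes.** The secondary list includes stoma complications over the long term, stoma-related readmissions, the reoperation rate, and survival free of hernia operation at 3 and 5 years. Readmissions and reoperations carry no time window.
- **Sample size.** The long-term allowance is "assuming a 5-year drop-out rate of 50%, 102 patients per group are needed". Neither the timing nor the causes of drop-out are given.
- **Data collection, management and analysis.** For patients who leave early, "Any data on a subject’s participation and procedures until the withdrawal will be analyzed within the research". Partial follow-up of unequal length therefore enters the analysis.

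**The concern.** These outcomes accrue between visits over as long as 5 years and are seen only until death, withdrawal or loss. A χ² or Fisher table needs each patient to be either with or without the event, out of a fixed number. A patient last seen event-free at 1 year fits neither cell for a 5-year outcome. Someone must choose whether to count that patient as event-free, leave the patient out, or keep only those who completed follow-up, and the article does not say which. The choice changes the reported risk.

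The article's Discussion and Conclusions make long-term effectiveness and safety of the mesh a main purpose, and the sample was doubled for it. The absolute risks of reoperation, readmission and stoma complication are what surgeons would use when advising patients. If drop-out differed between arms, the comparison itself would also be affected.

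**Working it through.** **Inputs from the article.** 102 per group, 50% drop-out by 5 years, visits at 30 days and at 1, 3 and 5 years. **Assumed, because the article does not give them:** the drop-out pattern, the event risks (10%, 15%, 20% at 5 years), the timing of events, and the share of drop-out that is death.

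**1. The plan's own figure.** The planning rates are given as "we estimated a 6.4% rate of PSH and 34% PSH on a CT scan for the PVDF-mesh group and control group". With two-sided α 0.05 and 90% power, the two-proportion formula gives 43 per group, or 50 with continuity correction. The article states 51, which is close enough. The allowance is 51 / (1 − 0.5) = 102. The sample size is not at issue.

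**2. Unobserved time.** For a constant drop-out hazard λ with half lost at 5 years, λ = ln 2 / 5 = 0.1386 per year. Mean observed time = (1 − 0.5) / 0.1386 = 3.61 years. Unobserved share = 1 − 3.61/5 = 27.9%.

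- Linear drop-out: mean time is 3.75 years, so 25.0% is unobserved.
- Drop-outs observed only to their last attended visit: about 36%.
- Shorter windows under the constant hazard: 0.6% at 30 days, 6.6% at 1 year, 18.2% at 3 years.

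**3. Effect of the denominator.** Let the event hazard be g = −ln(1 − p)/5 for a true 5-year risk p, with no deaths.

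- Observed events per randomised patient: e = g/(g + λ) × [1 − exp(−5(g + λ))].
- Event-free completers per randomised patient: s = exp(−5(g + λ)) = (1 − p) × 0.5.

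| True 5-year risk | All randomised: e | Shortfall 1 − e/p | Events kept, event-free drop-outs excluded: e/(e + s) |
|---|---|---|---|
| 10% | 7.3% | 27% | 13.9% |
| 15% | 10.9% | 27% | 20.4% |
| 20% | 14.6% | 27% | 26.8% |

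Example for 15%: g = 0.0325, so e = 0.0325/0.1711 × (1 − 0.425) = 0.109, and 0.109/(0.109 + 0.425) = 0.204.

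Completers only: 102 × 0.5 = 51 per group. This is unbiased only if drop-out is unrelated to outcome, and it discards about half the patients.

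**4. If half of the drop-out is death.** Death is then a competing event with hazard λ/2 = 0.0693. For the same g = 0.0325, the target is the cumulative incidence 0.0325/0.1018 × [1 − exp(−0.509)] = 12.7%. The all-randomised proportion is still 10.9%. Shortfall = 1 − 10.9/12.7 = 14%. If all drop-out were death, the shortfall would be zero.

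**5. If events come early.** Take events evenly spread within the first 30 days and evenly spread afterwards. The chance that an event is observed is 0.994 for the early ones and 0.717 for the later ones.

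- Half early: 0.5 × 0.994 + 0.5 × 0.717 = 0.856, a shortfall of 14%.
- 80% early: 0.8 × 0.994 + 0.2 × 0.717 = 0.939, a shortfall of 6%.

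**6. Between-arm contrast with equal drop-out (20% v 10%, all randomised, no deaths).** Observed 14.6% v 7.3%. The risk ratio goes from 0.50 to 0.497. The difference goes from 10 to 7.4 points, and power at 102 per group from 52% to 39%.

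**The case against.** The strongest reply is that the article never says drop-outs count as event-free.

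- **Denominator.** Intention-to-treat fixes the group in which a patient is analysed, not the outcome given to someone who was lost. Doubling 51 to 102 suggests that about 51 observed patients per group were expected at 5 years, and the imputation sentence treats lost outcomes as missing. This stands. A reader might infer that the outcomes will be tested as proportions of all 102 and that the rates will therefore be understated by 28%. The document supports neither the fixed denominator nor a single direction of bias.
- **Window.** Readmissions and reoperations have no stated window and could be meant as early outcomes. This stands too, so for those two the point applies only if they are counted over long-term follow-up.
- **Size.** Deaths among drop-outs and early events both shrink the bias, as steps 4 and 5 show. Combined, they would shrink it further.
- **The mixed model.** Complications are recorded at each visit, so stoma status could be fitted by the GLMM. That covers status at visits. It is not a stated method for readmissions and reoperations that happen between visits.
- **Imputation.** It is reserved for sensitivity analyses, so the main result remains the χ² or Fisher comparison.
- **Condensed article.** Fine detail may well sit in a fuller plan. But the article does state a test for categorical outcomes, and no fixed denominator makes that test suit events accruing over unequal follow-up. It also lists an operation-free survival outcome without naming any method for it.

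A reader might also infer that the mesh would be made to look safer than the control. With equal drop-out both arms are affected alike and the risk ratio is nearly unchanged, so that does not follow. Unequal drop-out could bias the comparison, but nothing in the article predicts it.

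**Conclusion.** The point holds in a limited form. For categorical outcomes that are not repeated measurements the article fixes only χ² or Fisher. It plans for half the patients to be lost by 5 years, keeps partial follow-up, and names no method that uses time at risk, even for operation-free survival.

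The direction of the error depends on a denominator that is not stated. If all randomised patients are counted, a 5-year risk of 10-20% is understated by about 27% in relative terms, given constant drop-out and event hazards and no deaths. The figure is about 14% if half of the drop-out is death or half of the events fall within 30 days, and about 6% if 80% are that early. If known events are kept and event-free drop-outs excluded, 15% becomes about 20%.

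Absolute risks and their difference are affected; with equal drop-out the risk ratio is not materially changed. The sample size and the 30-day outcomes are not touched by this point. The plan should be changed, because the remedy is cheap and long-term safety is a stated aim.

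**What to change.** Add to Statistical methods, for outcomes followed beyond 30 days (long-term stoma complications, hernia reoperation and operation-free survival, and readmissions and reoperations if counted over long-term follow-up):

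- State the time window of each outcome, in particular for readmissions and reoperations.
- Report the cumulative incidence of the first event at 1, 3 and 5 years, with censoring at last contact and death as a competing event, and give the between-arm difference with a 95% confidence interval. For operation-free survival, use Kaplan-Meier if death counts as an event.
- For repeat readmissions, use a Poisson or negative binomial model with log follow-up time as offset.
- Keep χ² or Fisher for 30-day outcomes such as Clavien-Dindo complications, where follow-up should be nearly complete.

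**Cost.** A few sentences in the plan, and event dates and a last-contact date for every patient. No extra visits or patients are needed. The 5-year confidence intervals will be somewhat wider than a simple proportion of 102 would suggest. Censoring at last contact still assumes that drop-out is unrelated to later risk, so the planned imputation remains useful as a sensitivity analysis.

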**Methods/design:**

The Chimney Trial is a Nordic, prospective, randomized controlled, multicenter trial designed to compare the feasibility and the potential benefits of specifically designed, intra-abdominal onlay mesh (DynaMesh®-Parastomal, FEG Textiltechnik GmbH, Aachen, Germany) against controls with permanent colostomy without mesh.

The primary outcome of the Chimney Trial is the incidence of a PSH detected by a computerized tomography (CT) scan at 12-month follow-up. Secondary outcomes are the rate of clinically detected PSHs, surgical-site infection as defined by the Centers for Disease Control and Prevention (CDC), complications as defined by the Clavien-Dindo classification, the reoperation rate, operative time, length of stay, quality of life as measured by the RAND-36 survey and colostomy impact score, and both direct and indirect costs. For each group, 102 patients were enrolled at attending hospitals and randomized at a ratio of 1:1 by browser-based software to receive a preventive mesh or a conventional colostomy without a mesh. Patients will be followed for 1 month and at 1, 3, and 5 years after the operation for long-term results and complications.

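### Randomisation is stratified by centre, but the named primary test ignores centre: valid, slightly conservative, and cheap to correct

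*Protocol article*

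**What the plan says.** Three places in the protocol article bear on this.

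- **Allocation:** "A separate randomization list is created for each center". Block sizes vary at random between two, four and six. The abstract adds that patients are "randomized at a ratio of 1:1 by browser-based software". Study setting names seven hospitals and expects more, and Recruitment sets a floor of 20 cases per hospital.
- **Statistical methods, test:** "The primary endpoint and other categorical data will be analyzed by the" χ² test or Fisher's exact test. No centre term or stratified test is named.
- **Statistical methods, intervals:** the primary endpoint is the "incidence of PSHs detected by CT scan with 95% confidence intervals for all groups at 1-year follow-up". This describes an interval for each arm's incidence. No between-arm measure is named.

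**The concern.** Blocking within centre makes the arms nearly equal in every hospital, so differences in hernia risk between hospitals add almost nothing to the between-arm comparison. An unstratified test still counts that variation as noise. Its variance is then too large, its true type I error falls below the nominal 5%, and some power is given away.

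Hospitals could plausibly differ here, since the surgeons differ and both laparoscopic and robotic routes are allowed. The test is stated outright in the article, so this concerns a choice already made and not a detail left open. What is at stake is modest: a somewhat blunted primary comparison, which matters most if the mesh works less well than the design assumes.

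**Working it through.** **1. The plan's own sample size.** Inputs: "we estimated a 6.4% rate of PSH and 34% PSH on a CT scan for the PVDF-mesh group and control group", and "Assuming α = 0.05 and power = 90%, we would need 51 patients per group". The two-sided formula with pooled variance under the null, with mean rate (0.064 + 0.34)/2 = 0.202 and difference 0.276, is

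n = [1.960 × √(2 × 0.202 × 0.798) + 1.282 × √(0.064 × 0.936 + 0.34 × 0.66)]² / 0.276² = (1.113 + 0.683)² / 0.0762 = 42.4, so 43.

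The continuity correction multiplies 42.4 by [1 + √(1 + 4/(42.4 × 0.276))]²/4 and gives 49.3, so 50. That is within one patient of the stated 51. Then 51/(1 − 0.5) = 102, as in "assuming a 5-year drop-out rate of 50%, 102 patients per group are needed". The sample size reproduces, and nothing below changes it.

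**2. Why the plain test is conservative.** With balance inside each centre, the true null variance is proportional to the average of p_k(1 − p_k) over centres, which equals p(1 − p) − Var(p_k). The plain test uses p(1 − p). For a centre standard deviation τ on the logit scale, Var(p_k) is roughly [p(1 − p)]²τ², so the variance ratio is about 1 − p(1 − p)τ². At p = 0.20 and τ = 0.5 this is 1 − 0.16 × 0.25 = 0.96. The critical value 1.96 then acts like 1.96/√0.96 = 2.00, a type I error of about 4.6%. At τ = 1.0 the approximation is too crude, so simulation is needed.

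**3. Simulation.** Assumptions: seven near-equal centres, exact balance within centre, normally distributed logit centre effects, marginal risks held at the stated values, χ² without continuity correction against Cochran-Mantel-Haenszel (CMH), and 400,000 trials per cell. τ is assumed, and so is the 34% against 20% scenario.

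| Setting | Test | τ = 0 | τ = 0.5 | τ = 1.0 |
|---|---|---|---|---|
| Type I error, 20% risk, 102 per group | χ² | 4.9% | 4.5% | 3.8% |
| | CMH | 5.0% | 4.9% | 5.0% |
| Power, 34% vs 6.4%, 51 per group | χ² | 95.9% | 95.8% | 95.7% |
| | CMH | 95.9% | 96.0% | 96.6% |
| Power, 34% vs 20%, 102 per group | χ² | 61.9% | 62.3% | 63.2% |
| | CMH | 61.9% | 63.8% | 68.4% |

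At 34% against 6.4% with 102 per group, both tests have about 99.9% power. Separate, shorter runs put the χ² type I error at 4.3 to 4.7% for τ = 0.5 and 3.8 to 4.0% for τ = 1.0.

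**4. Fisher's exact test.** It is named as the alternative and is more conservative for its own reasons. In 20,000 simulated trials with 102 per group, its type I error at 20% risk was 3.5%, 3.1% and 2.6% for τ = 0, 0.5 and 1.0. The 3.5% at τ = 0 reflects the exact test itself and not the missing strata. At the design rates the smallest expected event count is 51 × 0.202 = 10.3 per arm, so small counts would not push the primary analysis towards Fisher.

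**5. The between-arm interval.** If the design rates were observed, the Wald interval is 0.276 ± 1.96 × √(0.2843/n). This gives 17.3 to 37.9 points with 102 per group and 13.0 to 42.2 with 51.

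**The case against.** The strongest reply is that nothing in the protocol is wrong. The χ² test controls type I error, the loss at the planned effect is under 1 point, and the larger loss needs two assumptions that the protocol does not supply: a smaller effect and strong centre differences. All of that stands, and it is why the point is minor. It does not remove the point, because the change costs nothing. It also helps where the trial is least secure: the 6.4% comes from a case series of 31 patients, and the Introduction cites a randomised trial of another mesh technique with 32% against 34%.

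Three stronger readings are tempting, and the document does not support them.

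- **Inflated false positives.** The error runs the other way. The plain test rejects too rarely.
- **No interval for the mesh effect.** A reader might infer that the between-arm comparison will be lost because only per-group intervals are mentioned. The interval is merely not named. It follows from the same data, the analyses are to follow CONSORT, and a condensed article may leave the effect measure to the analysis plan.
- **RAND-36 analysed without its baseline.** A reader might infer this from "Analysis of variance (ANOVA) will be used for continuous variables". The next sentence assigns repeatedly measured continuous data to a linear mixed model, and Table 1 schedules RAND-36 at baseline, 30 days and 1, 3 and 5 years. ANOVA is left for outcomes measured once, such as operative time and length of stay. How baseline enters the mixed model is analysis-plan detail.

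**Conclusion.** The point holds as a mismatch between a centre-stratified design and an unstratified primary test. The named test is valid but conservative when centres differ, with a type I error of roughly 4 to 5% in place of 5%. The power given up is under 1 point at the design effect. For an assumed 34% against 20%, it runs from nothing with identical centres to about 5 points at a logit standard deviation of 1.0. These sizes rest on seven near-equal centres and on assumed heterogeneity. If the hospitals turn out alike, the two tests are practically the same. The impact is minor, and neither the sample size nor the validity of a positive result is in question.

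**What to change.** Before outcome data are examined, amend Statistical methods as follows.

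- Make the Cochran-Mantel-Haenszel test stratified by centre the single primary test.
- Report the Mantel-Haenszel risk difference with its 95% confidence interval alongside the incidence and interval in each arm.
- Fix in advance a rule for pooling very small centres. The protocol's own floor of 20 cases per hospital is a natural threshold.
- Keep the plain χ² or Fisher's exact test as a sensitivity analysis.

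The cost is protocol wording only. It needs no extra patients, data or change in sample size.
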